#### *Hamilton Depression Rating Scale- 17 *(HDRS-17)

The HDRS-17 is a widely used semi- structured clinical interview covering a range of affective, behavioral and biological symptoms and has acceptable psychometric properties [19]. Throughout the study all HDRS-17 interviewers will participate in ongoing training sessions and monthly consensus meetings supervised by an expert psychiatrist to maximize accuracy and consistency in the administration of the HDRS-17.

#### *The Patient Health Questionnaire-9 *(PHQ-9)

The PHQ is a relatively short self report version of the Primary Care Evaluation of Mental Disorders (PRIME-MD). The full PHQ screens for the five most common mental disorders using DSM-IV criteria: depressive disorders (MDD and dysthymia), anxiety disorders (panic disorder and generalized anxiety disorder), alcohol abuse, somatoform disorder, and eating disorders (bulimia nervosa and binge eating disorder) [18]. The PHQ-9 is the 9 item sub-scale for MDD [22].

### Secondary outcome measures

The secondary outcome measure is quality of life. It will be measured with the MOS-SF36, a short-form health survey consisting of 36 questions. It yields an 8-scale profile of functional health and well-being as well as a physical health and mental health summary scale and a preference-based health utility index. The MOS-SF-36 has been successfully used in surveys of general and specific populations, to compare the relative burden of diseases, and to assess and compare the health benefits produced by a wide range of different treatments [24].

### Power

Based on Scott *et al *[25] we expect a medium effect size (.50) [26] of bCBT as compared to GPC. With an alpha of 0.05 (one-sided) we will need 51 patients in each experimental condition to achieve a power of .80 [27].

When taking into account a refusal rate of .20 [25,28-30] we will need 61 patients per treatment condition, which implies a total sample size of 122 patients.

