### Primary outcome measures

Primary outcomes will be depressive symptomatology as measured by the patient rated PHQ-9 [22], depression severity as measured by the clinician rated HDRS-17 [19], the proportion of patients achieving response on the HDRS-17 and the proportion of patients achieving remission on the HDRS-17. In accordance with the National Institute of Mental Health criteria [23], response is defined as a ≥ 50% decrease of the baseline HDRS-17 score, remission is defined as a HDRS-17 score ≤7.

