### Treatment effect

To take potential biased outcomes caused by selective loss to follow-up into account we will use a generalized linear mixed model (GLMM) analysis approach, which, assuming missing at random (MAR) for missing values, gives unbiased effect estimates. MAR is a less restrictive assumption than missing completely at random and allows loss to follow-up to be related to baseline characteristics that are incorporated in the regression model. In all of these analyses intervention is the independent variable and a propensity score is entered as covariate to adjust for potential confounders. All analyses with dichotomous outcomes will be carried out with Generalized Estimating Equations (GEE).

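### The single stated power of .80 matches a comparison of means, but two of the four equally ranked primary outcomes are proportions, for which the same calculation gives less power

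*Protocol article*

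**What the plan says.** The Primary outcome measures section lists four primary outcomes and ranks none of them first: the PHQ-9 score, the HDRS-17 score, and then "the proportion of patients achieving response on the HDRS-17 and the proportion of patients achieving remission on the HDRS-17". Response is a fall of at least half from the patient's own baseline HDRS-17; remission is a score of 7 or less.

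The Power section expects a medium standardised effect of .50 for bCBT against GPC and continues: "With an alpha of 0.05 (one-sided) we will need 51 patients in each experimental condition to achieve a power of .80". After an allowance for refusal this becomes "61 patients per treatment condition, which implies a total sample size of 122 patients". The section names no outcome, test, visit, or response or remission rate.

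The Treatment effect section assigns dichotomous outcomes to GEE. The Assessments section plans three post-baseline visits, at 6, 12 and 52 weeks. The Objective section hypothesises that bCBT is superior, without saying which primary outcome decides this.

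**The concern.** A reader will take .80 as the power for the primary comparison, whichever of the four outcomes that is. The figure appears to come from a formula for means. Cutting a score into yes or no discards information, so the same number of patients gives less power for a proportion under the same underlying effect. This is separate from multiplicity, because it applies to each binary outcome tested alone.

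The stake is interpretation. If bCBT has exactly the assumed effect, a non-significant result on response or remission may be quite likely by design. With those outcomes on an equal footing with the scores, such a result could be read as evidence against superiority, or as contradicting the continuous scores.

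**Working it through.** **Inputs from the Power section:** effect size .50, one-sided alpha .05, power .80, 51 per arm, 61 per arm after the refusal allowance.

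**Step 1: reproduce the stated figure.** For a two-sample t-test with n per arm, the noncentrality is 0.50 × √(n/2) on 2n − 2 degrees of freedom. One-sided power at .05 is .799 for n = 50 and .806 for n = 51, so 51 is the first n that reaches .80. A two-sided test needs 64 per arm and has power .706 at 51, so it does not match. If .50 is read instead as Cohen's h for two proportions, n = 2 × (1.645 + 0.842)² / 0.25 = 49.5, that is 50, which also misses the printed 51. The comparison of means is the reading that fits.

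**Step 2: carry the same effect to a binary outcome.** Assumptions, none of them in the document: a normal score shifted by .50 SD, one common threshold, one visit, independent patients. If the GPC rate is p1, the bCBT rate is p2 = Φ(Φ⁻¹(p1) + 0.50). With p̄ = (p1 + p2)/2, one-sided power of the pooled test is

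Φ{ [ (p2 − p1) − 1.645 × √(2p̄(1 − p̄)/n) ] / √( [p1(1 − p1) + p2(1 − p2)]/n ) }.

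The best case is the symmetric cut, p1 = .401 and p2 = .599. At n = 51 this is (0.1974 − 0.1629)/0.0971 = 0.356, and Φ(0.356) = .639.

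| GPC rate | bCBT rate | Power, 51 per arm | Power, 61 per arm |
|---|---|---|---|
| 10% | 22% | .49 | .55 |
| 20% | 37% | .59 | .66 |
| 30% | 49% | .63 | .70 |
| 40% | 60% | .64 | .71 |
| 50% | 69% | .63 | .70 |
| 60% | 77% | .60 | .67 |
| 70% | 85% | .55 | .62 |

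Power of .80 at the best cut would need 79 per arm analysed.

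**Step 3: vary the assumptions, with 51 per arm.**
- Other tests at the best cut: .651 (unpooled), .631 (log-odds), .641 (arcsine).
- A logistic underlying scale, odds ratio exp(0.50 × π/√3) = 2.48: up to .73.
- .50 read as Cohen's h: .81.
- A common effect over three visits, the kind of contrast a GEE could test. With within-patient correlation ρ, the effective n per arm is 51 × 3/(1 + 2ρ). At the best cut:

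| ρ | Effective n per arm | Power |
|---|---|---|
| .3 | 95.6 | .87 |
| .5 | 76.5 | .79 |
| .7 | 63.8 | .72 |
| .8 | 58.8 | .69 |

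Repeated visits help the continuous scores too. With the same effective n, Φ(0.50 × √(n/2) − 1.645) gives about .97 at ρ = .3 and .86 at ρ = .8. The gap between the two kinds of outcome therefore remains.

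**The case against.** The Power section never attaches .80 to response or remission, and 51 is computed correctly for a comparison of means. This is not an arithmetic error, and that part of the objection stands. The t-test is an inference, since the section gives neither test nor scale. It is a close inference, because the main rival reading gives 50.

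A reader might go further and conclude that the GEE analyses of response and remission have at most about .64 power. The document does not support that. The .64 is the maximum for a two-proportion test at one visit, under a normal score with one common cut and 51 analysed per arm. It is not a GEE power. Three follow-up visits are planned, and a common effect across them could bring power near to or above .80 if the within-patient correlation is about .5 or lower. Neither the contrast nor the correlation is given. Response is a percentage change from each patient's baseline, so a common threshold only approximates it. No expected rates are given either.

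It can also be said that a condensed article may leave a separate power calculation for the binary outcomes to the full protocol. That would excuse the missing calculation alone. It does not settle the mismatch in the text as it stands, where four primary outcomes of equal rank share one power figure that fits two of them.

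**Conclusion.** The point holds in a limited form. The stated .80 with 51 per arm is supported for the PHQ-9 and HDRS-17 scores at an effect of .50. It is not shown for HDRS-17 response or remission.

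On the single-visit basis that the sample size appears to use, binary power falls short by about 16 to 31 percentage points (.64 to .49 against .80) over control rates of 10% to 70%. A true effect of the assumed size would then miss significance on a given binary outcome in more than one trial in three. These figures rest on the normal-score, common-threshold and single-visit assumptions and on 51 analysed per arm, so they illustrate the loss and do not bound it. What does not depend on the exact figure is that one power statement is being applied to outcomes that carry different amounts of information.

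**What to change.** In the Power section, state that .80 applies to the continuous HDRS-17 and PHQ-9 comparison at an effect size of .50, and name the test. Add that response and remission have lower power on that basis, giving the range .49 to .64 at 51 per arm together with its assumptions. Alternatively, give a GEE-based power with the expected rates, the contrast tested and the within-patient correlation stated.

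In the Primary outcome measures section, state that the superiority conclusion rests on the continuous score for which the trial was sized. Report response and remission as supportive estimates with confidence intervals, so that a non-significant responder result is not taken as absence of effect.

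The cost is a less favourable stated power for two outcomes and a lower standing for them. No extra patients, visits or data are needed.

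### The planned 122 patients fall slightly short of the plan's own requirement: a 20% loss from 61 per arm leaves about 49, not 51, and power of about 79%, not 80% (minor)

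*Protocol article*

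**What the plan says.** The Power section of the protocol article builds the sample size in two steps.

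- **Step 1.** For a medium standardised effect of .50 and a one-sided alpha of 0.05, it says "we will need 51 patients in each experimental condition to achieve a power of .80".
- **Step 2.** "When taking into account a refusal rate of .20", it continues, "we will need 61 patients per treatment condition, which implies a total sample size of 122 patients".

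The section does not give the formula used in step 2. It also does not say what the .20 counts: missing outcome data, refusal of the allocated treatment, or refusal to enter the trial.

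**The concern.** An allowance for loss should ensure that the number left after the loss is the number the power calculation needs. Here that number is 51 per arm, so 80% of the inflated figure should be at least 51. Eighty per cent of 61 is below 49. The three printed figures (51, .20 and 61) therefore cannot all hold together, and the trial's headline sample size does not deliver its stated power at its own assumed rate. At stake is the accuracy of the stated size and power; the planned analysis and its error rate are not affected.

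**Working it through.** **Inputs, all from the Power section:** standardised effect d = 0.50; alpha 0.05, one-sided; target power 0.80; equal arms; allowance 0.20; stated sizes 51, then 61 per arm (122 in total). One reading is needed: the .50 is taken as a standardised mean difference, which fits the continuous primary outcomes (PHQ-9 and HDRS-17 scores).

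**1. Reproduce the 51.** For a two-sample t-test with n per arm, power = P(T > t(0.95; 2n - 2)), where T is noncentral t with 2n - 2 degrees of freedom and noncentrality d x sqrt(n/2).

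- Solving for power 0.80 gives n = 50.15, rounded up to 51.
- n = 50 gives 0.799 and n = 51 gives 0.806.

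So the stated 51 is right, and it is the smallest whole number that reaches .80.

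**2. Reproduce the 61.**

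- 51 x (1 + 0.20) = 61.2, which rounds to 61.
- 102 x 1.20 = 122.4, which rounds to 122.

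Both printed figures agree with multiplication by 1.2. This is an inference, since no formula is given.

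**3. Apply the plan's own rate to the plan's own number.**

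- 61 x 0.80 = 48.8 per arm, against 51 needed.
- 122 x 0.80 = 97.6 in total, against 102 needed.
- Largest loss that still leaves 51: 1 - 51/61 = 0.164. The plan therefore tolerates 16.4%, not 20%.

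**4. Correct inflation.** 51 / (1 - 0.20) = 63.75, so 64 per arm and 128 in total. Check: 64 x 0.80 = 51.2. The shortfall is 128 - 122 = 6 patients (6/128 = 4.7%).

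**5. Is rounding the explanation?** No. Rounding 61.2 up gives 62, and 62 x 0.80 = 49.6, still below 51. Starting from 50 per arm, which the normal approximation gives in place of 51, 50 / 0.80 = 62.5, so 63 per arm; 61 is still too few.

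**6. Power at the number left** (d = 0.50, one-sided 0.05):

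| n per arm | t-test | normal approximation |
|---|---|---|
| 48 | 0.784 | 0.789 |
| 48.8 | 0.790 | 0.795 |
| 49 | 0.792 | 0.797 |
| 51 | 0.806 | 0.811 |
| 61 (no loss) | 0.865 | 0.868 |

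At the assumed loss, power is about 79%: about one point below the stated .80, and 1.6 points below the 80.6% that 51 per arm would give.

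**The case against.** **The effect is negligible.** One point of power is far inside the uncertainty of an effect size described only as medium. No estimate, test or error rate changes. This stands, and it is why the point is minor.

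**The 48.8 is close to a worst case.** It treats every lost patient as contributing nothing. The Assessments section plans measurements at 6, 12 and 52 weeks, and an exit assessment where possible for those who stop treatment. The Treatment effect section plans a mixed model that uses partly observed patients and adjusts for a covariate. As an illustration only, since the article gives no correlation, a covariate correlated 0.2 with the outcome has the effect of dividing n by 1 - 0.2² = 0.96: 48.8 / 0.96 = 50.8, which brings power back to about 0.80. This stands as a reason why the practical loss may be smaller still. It does not rescue the paragraph, which takes no credit for these features.

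**Refusal may mean refusal before randomisation.** The section on recruitment and baseline assessment does have patients decide on entry before the general practitioner randomises. Division by 0.80 is still the right operation on that reading: 61 approached would yield about 49 entered.

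**An article condenses a longer document.** That would excuse a missing formula. It does not excuse printed figures that disagree with one another.

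**Conclusion.** Wrong as written; severity minor. At the plan's own 20%, 61 per arm leaves about 49 evaluable and about 79% power, against the stated 51 and .80. The stated inputs require 64 per arm, 128 in total. This rests on reading .50 as a standardised mean difference, on a simple two-arm t-test, and on the .20 being a proportion of those counted in the 61. That the authors multiplied by 1.2 is likely but not documented; the finding does not depend on it, because 61 falls short however it was reached.

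Two stronger readings are tempting and should be resisted.

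- **That the trial is materially underpowered.** The figures show a gap of about one point at the assumed loss, and power above .80 if loss stays at or below 16.4%.
- **That the .20 are randomised patients who refuse their allocated treatment, so that an intention-to-treat analysis dilutes the effect well below .50.** The article does not say that the .20 has this meaning, and pre-randomisation refusal is also possible. Nor does it say whether the .50, taken from a cited study, already reflects incomplete uptake; if it does, reducing it again would count the same thing twice. No diluted effect can be derived from the document, so no power figure for one is offered here.

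**What to change.** Correct the second paragraph of the Power section in one of two ways.

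- **Keep 122 and restate what it delivers.** For example: *with a 20% loss, about 49 patients per arm are evaluable, giving about 79% power (one-sided 0.05)*. This costs wording only and is the proportionate choice for a one-point gap.
- **State 64 per arm, 128 in total,** as the number that the stated inputs require. If the trial recruits to it, the cost is six more patients.

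In the same edit, add a clause saying what the .20 counts. This is a clarification only and also costs wording alone.

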### Data analysis

We will compare the groups at baseline on socio- demographic characteristics, and functional and clinical data to check whether the randomization has been successful. The main analyses will be intention to treat.

### Treatment effect

To take potential biased outcomes caused by selective loss to follow-up into account we will use a generalized linear mixed model (GLMM) analysis approach, which, assuming missing at random (MAR) for missing values, gives unbiased effect estimates. MAR is a less restrictive assumption than missing completely at random and allows loss to follow-up to be related to baseline characteristics that are incorporated in the regression model. In all of these analyses intervention is the independent variable and a propensity score is entered as covariate to adjust for potential confounders. All analyses with dichotomous outcomes will be carried out with Generalized Estimating Equations (GEE).

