### Recruitment of patients and baseline assessment

GPs will be asked to include patients whom they consider to be suffering from MDD. Patients identified by their GP as suffering from MDD will receive information regarding the study and are asked to fill out the Patient Health Questionnaire (PHQ) [18]. Within 3 days after inclusion by the GP, a researcher will contact the patient by telephone to provide further explanation and seek informed consent regarding the diagnostic phase of the study. Consenting patients will be further assessed with a telephonic SCID-I interview. If the patient fulfills the DSM-IV criteria for MDD, subsequent SCID-I sections will be checked to assess eligibility. When eligible, the patient will be further assessed with a baseline Hamilton Depression Rating Scale-17 (HDRS-17) [19] to establish the severity of the depression. At the end of the telephonic assessment the patient receives the results of the interview and is asked to discuss these results and the treatment options with the GP. All results will also be sent to the GP. During the appointment with the GP the patient will make the decision to enter the trial or not. If the patient agrees to participate in the study, a second informed consent form will be signed and the GP proceeds with the randomisation procedure as described below.

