### Randomization

After informed consent, GPs will perform an internet based randomization procedure. A computer program generates a stratified block randomization (block randomization of 4 blocks stratified by gender and location (Nijmegen/Amsterdam)) where the patient is randomized over the two treatment strategies with no preference option. The computer then generates an outcome on the GP's computer screen and simultaneously sends an email of this outcome to the researcher. If the patient is randomized to GPC, the GP will immediately make the first appointment. If the patient is randomized to bCBT the researcher will contact the nearest participating FLP and refer the patient.

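### Every treatment-effect model adjusts for a propensity score of unstated content in a randomised trial, while the baseline outcome value and the stratification factors are not named as model terms

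*Protocol article*

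**What the plan says.** The Randomization section describes computer-generated block allocation, "stratified by gender and location (Nijmegen/Amsterdam"). The Recruitment section places the severity rating before allocation: "the patient will be further assessed with a baseline Hamilton Depression Rating Scale-17 (HDRS-17"). Under Data analysis the arms are compared at baseline "to check whether the randomization has been successful".

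The Treatment effect section plans a mixed model (GLMM), with GEE for dichotomous outcomes. It defends the mixed model by a missing-at-random (MAR) assumption that "allows loss to follow-up to be related to baseline characteristics that are incorporated in the regression model". It then fixes the adjustment for all the models: "In all of these analyses intervention is the independent variable and a propensity score is entered as covariate to adjust for potential confounders". It does not list what goes into the score, name any other baseline term, or say whether the study-entry assessment enters the mixed model as a repeated outcome.

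**The concern.** A propensity score models the probability of receiving a treatment. It is meant for settings where that probability depends on patient characteristics. Here allocation is randomised to two arms of equal planned size, so the true probability is one half for every patient. A fitted score can describe only chance imbalance.

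Chance imbalance matters in variables that predict outcome, and those are best entered directly. A treatment-prediction score weights each variable by how far it happens to differ between arms, not by how well it predicts depression at follow-up. Used alone, it can take the imbalance out of the estimate and still leave the prognostic variance in the residual. The reported standard error then does not match the real spread of the estimate.

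Three further points follow.

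- Gender and location shaped the allocation but are not named in the analysis.
- The MAR argument needs the characteristics that drive dropout to be in the model, and a score that predicts treatment does not stand in for them. This matters most for response and remission, two of the four primary outcomes. Ordinary GEE tolerates baseline-dependent loss only if the relevant covariates are in the mean model.
- With unlisted contents, the score leaves the analyst free to choose among versions that give different results.

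**Working it through.** **Inputs from the article.** The Power section says "we expect a medium effect size (.50"), with one-sided alpha 0.05, power 0.80 and 51 per arm. Working in SD units, SD = 1.

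**Assumed, because the article does not give them.** The baseline-outcome correlation rho (range 0 to 0.7) and the contents of the score.

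**1. Reproduce the plan's figure.** n per arm = 2(1.645 + 0.842)² / 0.50² = 2 × 6.185 / 0.25 = 49.5, so 50. The t-test gives power 0.799 at 50 and 0.806 at 51. The stated 51 reproduces, and it takes no credit for covariate adjustment.

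**2. What direct baseline adjustment offers.** The unadjusted SE is √(2/51) = 0.198. Adjustment multiplies it by √(1 − rho²). At rho 0.5 this is 0.866 × 0.198 = 0.171, and power by the normal approximation is 0.898.

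**3. What the score gives as sole covariate.** This was simulated with 51 per arm, blocks of 4 within sex by site, and 4,000 trials per setting. The outcome is continuous at one time point. The logistic score is built from baseline, sex, site and six non-prognostic covariates. It is compared with ANCOVA on baseline, sex and site.

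| rho | Score only: model SE | Score only: power | ANCOVA: model SE | ANCOVA: power | Power difference |
|---|---|---|---|---|---|
| 0 | 0.205 | 0.783 | 0.199 | 0.800 | 1.7 points |
| 0.3 | 0.204 | 0.784 | 0.189 | 0.826 | 4.2 points |
| 0.5 | 0.202 | 0.810 | 0.172 | 0.890 | 8.0 points |
| 0.7 | 0.199 | 0.868 | 0.142 | 0.966 | 9.8 points |

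The estimate is unbiased throughout. At rho 0.5 the true spread with the score is 0.179 against a model SE of 0.202 (0.202 / 0.179 = 1.13, or 13% too large), and one-sided type I error is 0.030. At rho 0.7 the figures are 0.148 against 0.199, with type I error 0.014. ANCOVA gives 0.046 and 0.048.

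A separate simulation at rho 0.5, with a score of baseline plus five non-prognostic covariates, gives SE 0.200 against a true 0.178, type I error 0.027 and power 0.82. Direct adjustment there gives 0.172 against 0.172, 0.046 and 0.89.

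**4. Sensitivity to the unstated contents, rho 0.5.**

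- Score of baseline alone: SE 0.172 and power 0.89, the same as ANCOVA.
- Score of baseline and strata: SE 0.178 and power 0.87, against 0.172 and 0.89.
- Larger score with baseline and strata also in the model: SE 0.178 and power 0.87, with type I error 0.046.
- Study-entry score as a repeated outcome with a common baseline mean, plus the six-covariate score: SE 0.174 against a true spread of about 0.19, with type I error about 0.06 to 0.07. Here the error runs the other way.

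**The case against.** The strongest reply is that the article condenses a fuller plan. It does not say that baseline severity, gender or location are left out. Its MAR sentence refers to baseline characteristics in the model, severity may be inside the score, and the study-entry assessment may be a repeated outcome. A reader might infer that the score is used *instead of* these variables, but the text supports only that they are not named. The full covariate list may fairly be left to the analysis plan. The propensity score itself cannot, because it is a stated method with a stated and mistaken purpose.

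A reader might also infer that the trial throws away power it has already paid for. It does not: the sample size is a plain two-group calculation, and power with the score stays at about 0.78 to 0.87 in these scenarios.

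Nor is it established that standard errors will be too large. That depends on the contents of the score and on rho, and the fourth case in the working reverses the direction. The planned longitudinal models with all visits, and the GEE analyses, were not simulated.

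On MAR, a likelihood-based mixed model also conditions on outcomes seen at earlier visits, so its validity does not rest on baseline covariates alone. That defence does not carry over to ordinary GEE.

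Finally, nothing in the article links the baseline comparison to the choice of what enters the score. The wording leaves that route open but does not plan it.

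**Conclusion.** The point holds as a flaw that should be fixed, not one that invalidates the trial. The stated reason for the propensity score does not apply under randomisation, its contents are open, and better covariates are at hand.

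If the score holds several covariates and is the sole adjustment at one time point, the cost at an assumed correlation of 0.5 is about 7 to 8 points of power, with one-sided type I error near 0.03 instead of 0.05. Over correlations from 0 to 0.7 the loss is about 2 to 10 points. With a score of baseline and strata only, or with baseline also in the model, it shrinks to about 2 points or less.

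Since planned power is roughly kept, what is lost is mainly a free gain in precision and correct calibration. The figures do not support claims of a biased estimate, an underpowered trial or intervals that are always too wide. For response and remission the concern rests on the MAR reasoning, not on a simulated size.

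**What to change.** Delete the propensity score and name the covariates. Suggested wording: *Each outcome model includes treatment, visit, treatment-by-visit, the baseline value of that outcome (baseline HDRS-17 for response and remission), gender and location.* If baseline is modelled as a repeated outcome, it should not also be entered as a covariate.

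Keep the baseline comparison descriptive, and state that it does not decide which covariates enter a model. If the score is retained for some reason, justify it, list its contents in advance, and enter baseline and strata alongside it.

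The cost is one or two sentences of analysis text. The baseline measures, gender and location are already collected, so neither the sample size nor the visit schedule changes.

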**Methods/Design:**

A randomized, multi-centre trial involving two intervention groups: one receiving brief cognitive behavioral therapy and the other receiving general practitioner care. General practitioners from 109 General Practices in Nijmegen and Amsterdam (The Netherlands) will be asked to include patients aged between 18-70 years presenting with depressive symptomatology, who do not receive an active treatment for their depressive complaints. Patients will be telephonically assessed with the Structured Clinical Interview for DSM-IV Axis I Disorders (SCID-I) to ascertain study eligibility. Eligible patients will be randomized to one of two treatment conditions: either 8 sessions of cognitive behavioral therapy by a first line psychologist or general practitioner's care according to The Dutch College of General Practitioners Practice Guideline (NHG- standaard). Baseline and follow-up assessments are scheduled at 0, 6, 12 and 52 weeks following the start of the intervention. Primary outcome will be measured with the Hamilton Depression Rating Scale-17 (HDRS-17) and the Patient Health Questionnaire-9 (PHQ-9). Outcomes will be analyzed on an intention to treat basis.

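### The MAR justification given for the mixed model does not carry over to the GEE planned for HDRS-17 response and remission, two of the four primary outcomes

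*Protocol article*

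**What the plan says.** The Primary outcome measures section names four primary outcomes: the PHQ-9 score, the HDRS-17 score, and "the proportion of patients achieving response on the HDRS-17 and the proportion of patients achieving remission on the HDRS-17". The last two are dichotomous and are cut from the HDRS-17 total.

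The Treatment effect section opens with the threat and the remedy: "To take potential biased outcomes caused by selective loss to follow-up into account we will use a generalized linear mixed model (GLMM) analysis approach". The reason given is that this approach, "assuming missing at random (MAR) for missing values, gives unbiased effect estimates". It adds that MAR is weaker than missing completely at random (MCAR), and explains that MAR "allows loss to follow-up to be related to baseline characteristics that are incorporated in the regression model". The only covariate named is a propensity score: "a propensity score is entered as covariate to adjust for potential confounders".

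The section closes with "All analyses with dichotomous outcomes will be carried out with Generalized Estimating Equations (GEE". It mentions no weighting, imputation or other handling of missing values for these outcomes. The abstract gives the visits: "Baseline and follow-up assessments are scheduled at 0, 6, 12 and 52 weeks following the start of the intervention". The Assessments section plans an exit assessment for patients who stop treatment, but only where one can be obtained.

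**The concern.** The paragraph claims a property for one method and then gives half of the primary outcomes to another method that does not share it in general. A mixed model fitted by likelihood uses the earlier scores of patients who later leave, so dropout that depends on those scores is covered under MAR if the model is right. GEE without weights or imputation solves moment equations on the records that happen to be observed, and has no such general cover.

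Dropout related to the week-6 score is plausible in a depression trial with visits at weeks 6, 12 and 52. The arms differ in provider and contact schedule, so the pattern could differ between them, although the document gives no evidence that it does. If it did, response and remission could be biased while the continuous HDRS-17 analysis of the same interviews was not. Primary outcomes derived from one scale could then disagree for reasons of method alone.

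**Working it through.** **No stated figure to reproduce.** The article gives no dropout rate, HDRS-17 mean or SD, or expected remission rate. The check is therefore an argument plus an illustration on assumed inputs.

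**1. What unweighted GEE needs.** Let Y be remission at week 12, R = 1 if it is observed, x the model covariates including arm, and μ(x) the true mean. With an independence working correlation, the equation solved is Σ R·x·(Y − μ(x)) = 0. It is unbiased if E[R(Y − μ) | x] = Cov(R, Y | x) = 0.
- MCAR, or R depending only on x: the covariance is 0, so GEE is valid.
- R depending on the week-6 score, which is correlated with Y given x: the covariance is generally not 0, so GEE is generally not valid. An exchangeable working correlation may reduce the bias but need not remove it.

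**2. Size with no true effect (all inputs assumed except the cut-off).** HDRS-17 means 17/13/11 and SDs 4.5/6/6.5 at weeks 0/6/12, correlation 0.6, identical in both arms. The cut-off of 7 is the article's. True remission = Φ((7 − 11)/6.5) = Φ(−0.615) = 27%. Dropout after week 6 is 20% per arm. Where it is selective, it is logistic in the week-6 score with slope 1 per SD.

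| Dropout pattern | Observed remission, bCBT v GPC | OR, unadjusted | OR, adjusted for baseline HDRS-17 | OR, HDRS-17 imputed by arm first |
|---|---|---|---|---|
| Worse patients leave both arms alike | equal | 1.00 | – | 1.00 |
| Worse leave bCBT only | 29.9% v 26.9% | 1.17 | 1.07 | 1.00 |
| Worse leave bCBT, better leave GPC | 30.1% v 23.1% | 1.42 | 1.20 | 1.00 |
| Worse leave GPC only | mirror of row 2 | 0.86 | 0.93 | 1.00 |

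Arithmetic from the rounded rates: row 2, (0.299/0.701)/(0.269/0.731) = 0.4265/0.3680 = 1.16; row 3, (0.301/0.699)/(0.231/0.769) = 0.4306/0.3004 = 1.43. The ORs in the table come from a separate run, and the differences in the second decimal are simulation error. Row 4 should be the reciprocal of row 2: 1/1.16 = 0.86.

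**3. Size with a true effect (a second set of assumptions).** Remission about 20% v 33% at week 12, about 20% dropout, 400,000 simulated patients, one baseline covariate in the model:

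| Dropout depends on | OR, full data | OR, unweighted GEE | OR, weighted GEE |
|---|---|---|---|
| Nothing (MCAR) | 2.12 | 2.13 | 2.12 |
| Baseline covariate in the model | 2.13 | 2.14 | 2.13 |
| Week-6 score, same direction in both arms | 2.10 | 2.05 | 2.11 |
| Week-6 score, opposite directions by arm | 2.11 | 2.95 | 2.10 |

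In the last row the OR is inflated by 2.95/2.11 = 1.40, close to row 3 of the first table. In a smaller run of that case the full-data OR was 2.06, independence GEE gave 2.85 and exchangeable GEE 2.46.

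**4. Scale against sampling error.** The article plans 61 per arm. If 80% are analysed, that is 61 × 0.8 = 48.8. With 27% remission, SE(log OR) = √(2/(48.8 × 0.27 × 0.73)) = √(2/9.62) = 0.46. The unadjusted biases are then ln 1.17/0.46 = 0.34 SE and ln 1.42/0.46 = 0.76 SE. The largest adjusted bias is ln 1.20/0.46 = 0.40 SE.

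**The case against.** - **GEE needs MCAR, so the protection is lost.** A reader might infer this, but it goes too far. GEE stays valid when dropout depends only on covariates in a correct mean model, and that is the case the section itself describes when it explains MAR. The protection is narrowed, not lost. How far it reaches depends on the covariates. Only a propensity score is named, for confounding, and nothing says that it captures the reasons for dropout.
- **The article does not say that the GEE is unweighted and unimputed.** This stands in part. A condensed article may leave the detail to a fuller plan, so the point cannot be that such handling has been ruled out. It rests on what is stated: a missing-data argument made for one method, and a different method fixed for all dichotomous outcomes.
- **Bias needs dropout that differs by arm.** This stands. With the same pattern in both arms the OR is 1.00 under no effect, and 2.05 against 2.10 with an effect. The documents give no evidence of a difference, so a reader should not conclude that the results will be biased.
- **All magnitudes are assumed.** This also stands. The article's 20% is a refusal rate in the Power section, not dropout after week 6, and exit assessments would recover some scores. The figure of 1.42 needs opposite mechanisms in the two arms and no baseline adjustment.
- **A logistic mixed model would settle it.** It would not. If the continuous week-6 score drives dropout, a model of dichotomised remission never sees that score. Fitted to the settings of the first table, a random-intercept logistic model gave 1.16, 1.34 and 0.86, against 1.16, 1.44 and 0.86 from available cases. It also changes the target to a subject-specific odds ratio. Part of the problem is therefore dichotomising before dealing with the missing values, not GEE alone.

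**Conclusion.** The point holds in limited form. The MAR argument that supports the mixed model does not extend to GEE without weighting or imputation when dropout depends on earlier observed post-baseline scores. This affects response and remission, two of four primaries. The PHQ-9 and HDRS-17 score analyses are not touched.

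The bias ranges from negligible (same dropout pattern in both arms) to material (patterns that differ by arm). Under the assumed null settings the unadjusted OR is about 0.86 to 1.42, and 0.93 to 1.20 after adjustment for baseline HDRS-17. These figures illustrate what is possible and do not forecast this trial. At the planned size even the largest is below one standard error, but it is systematic and avoidable. It should be fixed; it is not a fatal flaw.

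**What to change.** Replace the closing sentence of the Treatment effect section with wording such as: *Missing HDRS-17 totals will be multiply imputed separately by arm under MAR, from all observed HDRS-17 and PHQ-9 scores, gender and location. Response and remission will be derived from the imputed totals, analysed with logistic GEE in each imputed data set, and combined by Rubin's rules.* Any further covariate in the GEE should also be in the imputation model.

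An acceptable alternative is GEE weighted by the inverse probability of remaining in the study, with that probability modelled on earlier scores by arm. A logistic mixed model should not be offered as a substitute.

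The change costs a little more programming and needs no extra patients, visits or data. It should be settled before outcome data are examined.
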